### Sample size

Adults in the working population aged between 35 and 66 years will be recruited at all three sites. In a pilot study [8], our group was able to measure an improvement in function with the Disabilities of the Arm, Shoulder and Hand Outcome Measure (DASH) score (median 47 [mean 46 ± 20 SD] to median 34 [mean 32 ± 15 SD]). As a result of a power analysis based on these results, 26 patients per group will be required to achieve 80% power at a significance level of α = 0.05. With an expected drop-out rate of 10%, a total of 60 patients should be recruited, comprising 20 patients at each of the 3 sites.

Inclusion criteria for both groups will be surgical treatment of the shoulder joint after upper arm fracture classified as AO Foundation/Association for the Study of Internal Fixation (Arbeitsgemeinschaft Osteosynthese; AO) type 11 [10]. Participants will be included between the fourth and seventh weeks after surgery. The participant population will be stratified by fracture location (subcapital/capital) and handedness.

Exclusion criteria will be determined during baseline assessment. Participants with limited cognition as defined by a score < 10 points on the Short Orientation-Memory-Concentration Test (SOMC), inadequate level of pain during movement of the affected shoulder joint (pain score > 5 on a pain visual analogue scale [VAS]), strongly limited vision or hearing, heart failure (New York Heart Association stage III-IV), chronic obstructive pulmonary disease with Global Initiative for Chronic Obstructive Lung Disease (GOLD) stage III-IV, walking speed < 0.8 m/second, isolated tuberculum majus fracture of the humerus (AO 11, A1), or fractures with involvement of the glenoid cavity, as well as double fractures or injury of the plexus or the axillary nerve, will be excluded. All participants will give their written informed consent to the study administrators at each centre prior to the clinical baseline assessment.

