### Statistics

The centre and the number of treatment units will be regarded as possible covariates for the primary outcome. All data assessed will be described descriptively (mean, SD, 95% CI and median for metric variables; frequency and percentile for categorical variables). After checking the data for normal distribution by comparing the distribution histograms and Shapiro-Wilk test, the group comparison will be carried out with the *t* test or the rank-based Wilcoxon test. For the primary outcome analysis of covariance with study centre, number of therapy units (to take account of the training inhomogeneity) and injury severity (to take account of the patient’s homogeneity) as covariates will be performed. The secondary outcome (WMFT) will be analysed to generate study hypotheses using the methods described above. Inferential statistics will follow an intention-to-treat approach with mean imputation or regression imputation for all randomised patients with incomplete datasets if deemed necessary. Per-protocol analysis will be performed for evaluation of the efficacy of the intervention in patients with complete datasets and without protocol violations.

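### The intention-to-treat analysis may fill missing DASH outcomes with a mean or a regression prediction, which either understates the standard error or shrinks the estimated effect

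*Protocol article*

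**What the plan says.** The Statistics section sets the rule in one sentence: "Inferential statistics will follow an intention-to-treat approach with mean imputation or regression imputation for all randomised patients with incomplete datasets if deemed necessary". It permits two methods. It does not say whether the mean is per arm or overall, or whether arm enters the regression. It mentions neither multiple imputation nor a variance correction.

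The primary model is given just before: "For the primary outcome analysis of covariance with study centre, number of therapy units" and injury severity. The only analysis described as restricted to complete data is a different one: "Per-protocol analysis will be performed for evaluation of the efficacy of the intervention in patients with complete datasets and without protocol violations". It also removes protocol violators, so it is no complete-case check on the intention-to-treat result.

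The one figure for missing data is in the Sample size section: "With an expected drop-out rate of 10%, a total of 60 patients should be recruited".

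**The concern.** A value filled in with a mean carries no information, yet the analysis counts it as a measured patient. Two things can then go wrong, depending on which mean is used.

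- **Mean of the patient's own arm.** The filled values sit at the arm mean, the residual variance falls, and the sample looks complete. The interval is too narrow and the test rejects too often.
- **Overall mean.** The filled values are the same in both arms and pull the arms together. The estimated difference is too small.

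A regression prediction used without added noise behaves like the first if arm is a predictor and like the second if it is not.

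This concerns the inference on the primary outcome in a trial of 60 patients, where drop-out is expected. The article names the methods, so the point does not rest on something left unsaid.

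**Working it through.** **Inputs from the documents.** Pilot DASH: "median 47 [mean 46 ± 20 SD] to median 34 [mean 32 ± 15 SD", a difference of 46 − 32 = 14. Planning statement: "26 patients per group will be required to achieve 80% power at a significance level of α = 0.05". Drop-out 10%, 60 patients, hence 30 per arm.

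**The plan's own figure.** Pooled SD = √((20² + 15²)/2) = √312.5 = 17.68. With a two-sided α of 0.05 (sidedness is not stated, but this choice reproduces the number), n = 2 × (1.960 + 0.842)² × (17.68/14)² ≈ 25.03, rounded up to 26 per group. By t test, power at 26 is 80.0%. Inflating for drop-out gives 52/0.9 = 57.8, so 58, which the plan states as 60. The sample size reproduces. The 14 points are a pre-to-post change in the pilot and serve here only as a reference difference.

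**Arm-mean imputation, by formula.** Let p be the missing fraction and n the number per arm.
- True variance of an arm mean: s²/(n(1 − p)).
- Reported variance: filled values add nothing to the sum of squares, so the SD² falls to about (1 − p)s², and the divisor is n. This gives (1 − p)s²/n.
- Ratio of reported to true SE: √((1 − p)²) = 1 − p.
- At p = 0.10 the effective critical value is 1.96 × 0.9 = 1.76, a two-sided error of 7.8%.

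In figures, with 27 of 30 observed per arm: true SE = 17.68 × √(2/27) = 4.81. The reported variance is multiplied by 52/58 = 0.897 (the observed-data degrees of freedom over the apparent ones), so the reported SE = 17.68 × √0.897 × √(2/30) = 4.32. The ratio is 0.90.

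**Overall-mean imputation, by formula.** A fraction p of each arm has the same value, so the expected difference is (1 − p) × 14: 12.6, 11.2 and 9.8 at 10%, 20% and 30% missing.

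**Simulation within an analysis of covariance.** 30 per arm, SD 17.68, true difference 0 or 14, and one baseline covariate. Assumptions not in the documents: covariate–outcome correlation 0.5, outcomes missing completely at random, equal missingness in both arms. Only the 10% row has a basis in the plan; 20% and 30% are assumed scenarios. In the no-difference scenario there were 15,000 runs at 10% missing and 6,000 at 20% and 30%; with a 14-point difference, 3,000 runs; for multiple imputation, 1,500 throughout.

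| Method | Missing | Reported SE / true SD of estimate | Type I error | Estimate when truth is 14 |
|---|---|---|---|---|
| Arm mean | 10% | 0.89 | 8.0% | 14.1 |
| | 20% | 0.79 | 11.7% | 14.1 |
| | 30% | 0.70 | 16.5% | 14.1 |
| Regression with arm, no noise | 10% | 0.89 | 8.0% | 14.1 |
| | 20% | 0.79 | 11.6% | 14.1 |
| | 30% | 0.70 | 16.9% | 14.1 |
| Overall mean | 10% | 0.99 | 5.1% | 12.7 |
| | 20% | 1.00 | 4.8% | 11.3 |
| | 30% | 1.01 | 4.4% | 9.9 |
| Regression without arm, no noise | 10% | 0.99 | 5.0% | 12.6 |
| | 20% | 1.00 | 4.6% | 11.2 |
| | 30% | 1.01 | 4.7% | 9.8 |
| Multiple imputation with arm | 10% | 0.99 | 5.4% | 14.2 |
| | 20% | 1.02 | 4.3% | 14.0 |
| | 30% | 1.01 | 4.6% | 14.1 |

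The multiple-imputation error rates carry a simulation error of about 0.6 points. Complete-case analysis of covariance gave 5.0% type I error at 10% missing, so it is also valid under these assumptions.

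Arm-mean imputation also hides the information lost. With a true 14-point difference it rejected in 92.8%, 92.6% and 91.7% of runs as missingness rose, while complete-case analysis fell from 90.1% to 87.0% to 81.4%.

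**The case against.** The strongest reply is that a reader might infer more than the text supports, in three ways.

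**That the primary p-value and interval will be wrong under any permitted variant.** This does not follow. The rule allows no imputation at all, and it allows the overall mean. In a t-test simulation at 10% missing, overall-mean imputation rejected as often as complete-case analysis: 4.9% against 4.9% with no difference, 81.8% against 81.8% at 14 points. There the harm is to the estimate and to where the interval is centred. The test is anti-conservative only when arm enters the imputation.

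**That the variants push the result in opposite directions.** They do not. One leaves the estimate unbiased and overstates precision; the other attenuates the estimate and leaves significance about where it was. These are two separate faults.

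**That the plan is single imputation throughout.** This is certain only for mean imputation. Regression imputation usually means a single prediction, but the wording does not shut out a stochastic or multiple version.

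Two further points stand in part. The choice between methods and the trigger for imputing could be settled in an analysis plan that is not shown, so their openness is weak as a separate fault. The wording also speaks of incomplete datasets, which may include missing covariates or single DASH items; the figures above cover only wholly missing outcome scores.

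None of this rescues mean imputation of the outcome, which the article expressly allows.

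**Conclusion.** The point holds in this limited form. The article permits mean imputation for the intention-to-treat inference, and both readings of it are faulty when the primary outcome is missing. At the planned 10% drop-out, the per-arm version gives a type I error of about 8% instead of 5%, and the overall version takes about 1.4 of 14 points off the estimate (14 × 0.10). Deterministic regression imputation does the same, with and without arm respectively.

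At 20% and 30% missing, which are assumed and not planned, the figures are about 12% and 17% type I error, or effects of about 11.2 and 9.8 points. All sizes assume outcomes missing completely at random and equally in both arms; the simulated ones also assume a covariate correlation of 0.5.

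The harm is moderate at the planned drop-out. The wording should be corrected, but the point does not undermine the design or the sample size.

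**What to change.** Delete mean imputation and the clause that makes imputation depend on perceived need, and pre-specify one valid method before the data are seen.

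- **Preferred.** Keep the analysis of covariance as the primary model and use multiple imputation, with arm, baseline DASH, centre, the other covariates of that model and the later DASH scores in the imputation model, combined by Rubin's rules. The DASH is already scheduled at follow-up 1 and at 3, 6 and 12 months, so no new data are needed.
- **Acceptable alternative.** A likelihood-based mixed model over the scheduled DASH visits. This replaces the planned model, so the plan would have to say how injury severity and number of therapy units enter. It would also have to name the primary time point, which the article does not do.

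The cost is a change of wording, a little more analysis work and a wider interval. In the simulation at 10% missing with no true difference, the mean standard error was 4.19 under multiple imputation and 3.82 under arm-mean imputation, about 10% wider (4.19/3.82 = 1.10). The extra width is uncertainty that mean imputation leaves out. Recruitment stood at 50% when the article was published, so at that stage the wording could still be corrected before the final analysis.

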## Discussion

PHFs are often associated with immobilisation of the affected arm, leading to functional loss, pain and psychosocial problems. The aim of rehabilitation is to reintegrate the patient as quickly as possible into daily routine and work after surgical treatment. This study protocol describes an experimental set-up allowing the analysis of an additive robot-assisted training in combination with conventional occupational and physical therapy in comparison with conventional occupational and physical therapy alone. The robot-assisted training will allow the patient to mobilise the affected arm earlier and thereby to lose less muscle mass and improve motor capacity. This will be measured objectively with the WMFT-O and subjectively with the self-completed DASH questionnaire. This will possibly allow for an earlier return to work.

To the best of our knowledge, this is the first controlled study in the field of rehabilitation of PHFs using robot-assisted training. The results of the study will give insight into treatment modalities after PHF and into restoration of shoulder function. This will be important for learning about ways to improve therapy in terms of duration, intensity, frequency and extent. New ways will be needed also to improve commitment to therapy. Therefore, the robot-assisted approach will be an option to offer more effective rehabilitation early after surgery.

### Limitations

The sample size is relatively small and powered only for a functional endpoint (DASH). Social or economic endpoints such as return to work or cost-effectiveness of this intervention would require larger sample sizes and were not the purpose of this early-stage RCT. Furthermore, the set-up with three different associated centres will lead to some difficulties in the standardisation of the assessments. It is expected that different observers and therapists in the three institutions have subjective differences in the accomplishment of the tests. Assessment of the WMFT will be videotaped to standardise this as much as possible.

Heterogeneous treatment modalities will also exist to some extent for rehabilitation after PHF in the conventional occupational and physical therapy in terms of duration, intensity and frequency. Theoretically, participation in the robotic group could lead to increased or decreased motivation to participate in other types of exercises. Adherence will therefore be documented.

For dissemination the full and optimised training protocol will be provided via an online research platform. Also two videos, one about the instructions of the WMFT-O and one about the rating, are provided on YouTube (https://www.youtube.com/watch?v=8yDcWK9Xrtw, https://www.youtube.com/watch?v=MsfrGauYHfc).

## Conclusions

The results of the present RCT might help researchers in designing new therapeutic interventions in the rehabilitation of humeral fractures.

### Trial status

Patient recruitment was at 50% at the time of publication of this article.

## Abbreviations

AO: AO Foundation/Association for the Study of Internal Fixation (Arbeitsgemeinschaft Osteosynthese)
DASH: Disabilities of the Arm, Shoulder and Hand Outcome Measure
ED: Emergency department
GOLD: Global Initiative for Chronic Obstructive Lung Disease
PHF: Proximal humeral fracture
RCT: Randomised controlled trial
REDCap: Research Electronic Data Capture
ROM: Range of motion
SOMC: Short Orientation-Memory-Concentration Test
VAS: Visual analogue scale
WMFT: Wolf Motor Function Test
WMFT-O: Wolf Motor Function Test–Orthopaedic version
